### Secondary outcome measure

2.11

#### Change in menstrual frequency

2.11.1

The proportion of participants who have at least a 50% increase from baseline in monthly menstrual frequency to 3 months postintervention follow-up, and the change in monthly menstrual frequency from baseline, to after 3 months of intervention, and 3 months postintervention follow-up.

#### Change in anthropometry

2.11.2

The change in measurements for height, weight, waist and hip circumference, body mass index (BMI), and waist-hip ratio (WHR) at month 3 and 6. BMI is calculated by dividing the weight by the square of the height. WHR is calculated by dividing the circumference of the narrowest point of the waist by the circumference of the widest point of the hip.

#### Change in serum hormone level

2.11.3

The change in serum luteinizing hormone (LH), serum follicle-stimulating hormone (FSH), LH/FSH ratio, testosterone (T), estrogen (E), prolactin (PRL), progesterone (Prog), dehydroepiandrosterone (DHEA), sex-hormone binding globulin (SHBG), and androstenedione (AND) from baseline at month 3 and 6. Blood samples will be taken at menstrual cycle days 2 to 4 when ovulation or bleeding occurs. Otherwise, this will be performed on the arbitrary day of the cycle.

#### Change in ovarian morphology

2.11.4

Calculation changes in bilateral ovaries, mean difference in ovary volume, thickness of the endometrium, and the number of follicles <9 mm by ultrasonography from baseline at month 3 and 6.

#### Change in hirsutism and acne

2.11.5

Change in FG ^[22]^ and GAGS^[23]^ scores from baseline measured at month 3 and 6. The FG score assesses the hair growth of nine anatomic sites, and has a maximum score of 36 with a scale of 0 to 4 for each site. GAGS evaluate 6 locations, including the forehead, right cheek, left cheek, nose, chin, and chest or upper back. A local score is rated with a factor (1–3 scale) specific to the acne location, multiplying the grade on the acne of this location (0–4 scale). The global score is the summation of all local scores.

#### Change in anxiety and depression

2.11.6

The score of the Hospital Anxiety and Depression Scale (HADS)^[27]^ changed from baseline at month 3 and 6. HADS is validated and standardized for measuring the state of anxiety and depression.^[28]^ HADS has 2 subscales with 14 items (7 items each), and a total score of 0 to 21 with 0 to 3 for each item. A score of ≥8 shows the presence of anxiety and/or depression.

#### Change in quality of life (QOL)

2.11.7

The change in Polycystic Ovary Syndrome Questionnaire (PCOSQ)^[5]^ scores from baseline at month 3 and 6. PCOSQ has 26 questions and includes 5 domains, which are emotions, body hair, weight, infertility, and menstrual problems. A lower score indicates a more impaired QOL.^[29]^

#### Blinding assessment

2.11.8

Participants will answer the following questions after 12 weeks of intervention, in order to assess the blinding: “Do you think you have received traditional acupuncture in the past weeks?” The participants can answer “Yes,” “No,” or “Unclear.”

#### Expectation value of the acupuncture effect assessment

2.11.9

Participants will answer the following questions before the intervention: “Do you think acupuncture will be effective for treating the disease?” “Do you think acupuncture will be effective for improving the related symptoms of PCOS?” The participants can answer “Yes,” “No,” or “Unclear.”

#### Safety assessment

2.11.10

All adverse reactions will be presented in tables with a description on the categories, severity, rate of incidence, and correlation with the treatment. Adverse reactions related to acupuncture (severe pain, local hematoma, infection and abscess, and retained needle and broken needle during the treatment), including some discomforts after treatment, will be recorded in time in detail. Adverse events irrelevant with the treatment will also be recorded in detail.

### Statistics

2.12

#### Sample size

2.12.1

The calculation of the sample size was based on the primary outcome, which is the proportion of participants with at least a 50% increase from baseline in monthly menstrual frequency during the 12-week intervention.

According to 1 previous study,^[16]^ 38% of participants had increased menstrual frequency after 14 sessions of electro-acupuncture, and the proportion of participants with at least a 50% increase from baseline to 12 weeks was assumed to be 35% in the acupuncture group and 15% in the sham-acupuncture group. Each group sample size of 71 achieves 80% power to detect a difference between group proportions of 20%. A total of 172 participants (86 participants in each group) will be required for the study, with an alpha risk of 5% and a beta risk of 20%, assuming 20% loss to follow-up.

#### Statistical analysis

2.12.2

Data will be analyzed using SPSS software V.20.0 (IBM SPSS Statistics; IBM Corp, Somers, NY), based on the intention-to-treat (ITT) principle. Missing data will be calculated using the actual observational value instead of the method last observation carried forward. For continuous data, the data will be presented as mean ± standard deviation when normally distributed, or be presented as median (interquartile range) when not normally distributed. Statistical comparisons will be performed by Student *t* test and Wilcoxon rank sum test for continuous data and by *X*^*2*^-test for categorical data. The difference between groups will be analyzed by *X*^*2*^-test or Wilcoxon rank sum test. A *P* value <.05 will be considered statistically significant. The phenotypic distribution will be analyzed according to the included participants, and a subgroup analysis will be conducted according to these phenotypes. Moreover, the phenotypes of these participants will be divided into polycystic ovaries combined with oligo/amenorrhea and hyperandrogenism, oligo/amenorrhea and hyperandrogenism combined with polycystic, and oligo/amenorrhea combined with polycystic ovaries.

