#### Primary outcome measure

2.10.1

The proportion of participants who have at least a 50% increase from baseline in monthly menstrual frequency after 3 months of intervention.

Baseline monthly menstrual frequency was calculated through the number of menstrual bleeds in 3 months before intervention divided by 3. Monthly menstrual frequency from baseline to 3 months was calculated through the number of menstrual bleeds during the 3-month intervention divided by 3.

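### The planned tests ignore baseline although response on the primary outcome is defined from it: valid, but inefficient, and cheap to improve

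*Protocol article*

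**What the plan says.** **Tests (Protocol article, Statistical analysis, 2.12.2).** Comparisons use Student t "test and Wilcoxon rank sum test for continuous data and by" chi-square for categorical data. The next sentence assigns the between-group difference to chi-square or the rank-sum test and leaves the t test out. Neither sentence mentions a baseline covariate, a stratified test or a regression model.

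**Primary outcome (2.10.1).** A responder has a rise of at least 50% in monthly menstrual frequency over her own baseline. "Baseline monthly menstrual frequency was calculated through the number of menstrual bleeds in 3 months before intervention divided by 3"; the intervention period is counted in the same way.

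**Secondary outcomes (2.11.1 to 2.11.7).** These are changes from baseline, for example "the change in monthly menstrual frequency from baseline, to after 3 months of intervention, and 3 months postintervention follow-up". Anthropometry, hormones, ovarian morphology, hirsutism and acne, anxiety and depression, and quality of life are all measured at baseline and at months 3 and 6.

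**Sample size (2.12.1).** The responder proportion "was assumed to be 35% in the acupuncture group and 15% in the sham-acupuncture group". From these two rates the article derives 71 evaluable women per arm for 80% power, with no reference to baseline count.

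**The concern.** The denominator of the primary response is a small whole number, so the hurdle varies sharply between women. The inclusion criteria admit oligomenorrhoea and amenorrhoea, so baseline counts from 0 upwards will occur. A woman with 3 baseline bleeds can hardly respond, while a woman with 1 needs only one more. Baseline count should therefore predict response whatever the treatment, and the planned analysis does not use it. Likewise, comparing raw change scores leaves unused the information that a baseline covariate would supply. The stake is precision: the same patients and data could give a narrower interval and usually a more powerful test.

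**Working it through.** **1. Threshold by baseline count (from 2.10.1).** Response requires a follow-up count of at least 1.5 × baseline, in whole bleeds:
- baseline 1: 1.5, so 2 bleeds
- baseline 2: 3 bleeds
- baseline 3: 4.5, so 5 bleeds
- baseline 0: a percentage rise is undefined

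That the threshold depends on baseline follows from the definition. How strongly response depends on it does not, because the article gives neither the baseline distribution nor response by baseline count.

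**2. The plan's own figure.** Inputs from 2.12.1: 0.35 vs 0.15, alpha 5% (taken as two-sided, which is not stated), power 80%.
- Unpooled: n = (1.96 + 0.84)² × (0.35×0.65 + 0.15×0.85) / 0.20² = 7.85 × 0.355 / 0.04 = 69.7, so 70.
- Arcsine formula: 71. Pooled formula: 73.
- Exact power of the uncorrected chi-square at 71 per arm: 80.4%.

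The stated 71 per arm is reproduced for the unadjusted test.

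**3. Stratified test on the same endpoint.** Simulation with 40,000 runs per scenario, 71 per arm and overall rates held at 15% and 35%. The test is Cochran–Mantel–Haenszel (CMH), stratified on baseline count 0/1/2/3. Assumed shares of women at 0/1/2/3 bleeds: 25/35/30/10%. Check, strong scenario, sham: 0.25×0.425 + 0.35×0.092 + 0.30×0.037 + 0.10×0.004 = 0.150.

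| Assumed dependence | Sham response at 0/1/2/3 | Chi-square | CMH | Difference |
|---|---|---|---|---|
| none | 0.15 throughout | 80.3% | 79.0% | -1.3 |
| mild | 0.218/0.148/0.119/0.079 | 80.5% | 79.9% | -0.5 |
| moderate | 0.321/0.134/0.071/0.018 | 80.3% | 83.9% | +3.6 |
| strong | 0.425/0.092/0.037/0.004 | 80.7% | 89.5% | +8.8 |
| very strong | 0.529/0.038/0.015/0.001 | 80.0% | 96.5% | +16.5 |

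Merging counts 2 and 3 into one stratum makes practically no difference to these results.

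**4. A bleed model using the thresholds in step 1.** Monthly bleeding probability is beta-distributed between women and counts are binomial over 3 months, again calibrated to 15% and 35%. Chi-square stays near 80%. CMH power depends on how zero-baseline women are handled:
- any bleed counts as response: 80–87%
- zero-baseline women excluded: 82–86%
- zero-baseline women can never respond: 89–99%

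The last case partly reflects the calibration. If many women cannot respond, the others must carry the whole 20-point difference. In the most extreme setting, 55% have no baseline bleed and those with 1 must respond at 95% vs 43%.

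**5. Continuous outcomes.** With equal variances and baseline/follow-up correlation r, the change-score variance is proportional to 2(1−r) and the ANCOVA variance to 1−r². The ratio is (1−r²)/(2(1−r)) = (1+r)/2. No r is given, so a range is assumed. If the t test on change has 80% power, ANCOVA has Φ(2.80/√ratio − 1.96):
- r = 0.3: ratio 0.65, variance 35% lower, power about 94%
- r = 0.5: ratio 0.75, variance 25% lower, power about 90%
- r = 0.7: ratio 0.85, variance 15% lower, power about 86%

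**The case against.** The strongest reply is that nothing here is wrong. Under randomization the chi-square already allows for chance imbalance in baseline count, its type I error is sound, and it is the test that sized the trial. That stands.

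The gain on the primary also rests on assumptions: it vanishes if baseline count is not prognostic, and it moves with the unsettled rule for zero-baseline women. That stands too, so the size can only be given as a range. For the secondaries, change scores already use baseline in part, and these outcomes did not size the trial.

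Finally, the article is condensed, and an unseen analysis plan may add adjusted analyses. It may, but this section states which tests will be used, and all of them are unadjusted.

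A reader might go further in four ways that the document does not support:
- **That the choice of test costs the trial its stated power.** It does not: 71 per arm gives about 80% with the planned test. The allowance "assuming 20% loss to follow-up" is a separate matter: 86 × 0.8 = 68.8, about 69 per arm, with 78–79% power.
- **That chance imbalance biases the result.** It adds random error, which the unadjusted test already counts.
- **That baseline adjustment is possible for all outcomes.** Adverse reactions and the post-treatment blinding question have no baseline value.
- **That allocation is unstratified.** The randomization section mentions no stratification, but a condensed article may omit it.

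**Conclusion.** The point holds as one of efficiency. The plan fixes unadjusted tests while the primary response depends by construction on a baseline count that has to be collected anyway. Adjusting for it is worth roughly -1 to +10 points of power at the planned 35% and 15%. Larger gains appear only under very strong dependence or if zero-baseline women can never respond. The loss, if baseline count is not prognostic, is about 1 point. For the continuous secondaries the variance falls by 15–35% if r lies between 0.7 and 0.3. The direction follows from the outcome definition and from algebra; the sizes rest on an assumed baseline distribution and an assumed r. The change is advisable, but the planned analysis would not give an invalid answer without it.

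**What to change.** 1. First settle how a woman with zero baseline bleeds is classified, since her percentage rise is undefined. The endpoint needs this rule whatever the test.
2. Prespecify the primary analysis as a Cochran–Mantel–Haenszel test with a stratum-adjusted risk difference and 95% confidence interval, stratified by baseline bleed count (0, 1, 2 or more). Keep the raw chi-square as supportive, so that the link to the sample-size basis remains.
3. Analyse the continuous secondaries at months 3 and 6 by ANCOVA or a mixed model with the baseline value as covariate, in place of t or rank-sum tests on change scores.

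The cost is revised wording in the analysis section plus the rule in item 1. No extra participants, visits or measurements are needed. The change should be fixed before unblinding, because an adjustment added afterwards would look data-driven.

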## Discussion

3

The aim of this study is to evaluate the efficacy and safety of acupuncture for improving menstrual frequency and other symptoms of patients with PCOS. Previous studies have shown that acupuncture can modulate endogenous regulatory systems, including the sympathetic nervous system, endocrine system, and neuroendocrine system.^[30]^ Some studies have also found that acupuncture might be effective for menstrual frequency, improving ovulation rate and serum hormone level.^[31–33]^ Moreover, menstrual irregularity or amenorrhea may increase endometrial proliferation, which is related to potentially premalignant disorders.^[34]^ Therefore, the choice of acupuncture may provide an alternative means for women with PCOS who are not willing to be pregnant, and only want to improve their symptoms. According to a systematic review, no studies have reported the comparison of acupuncture to sham-acupuncture in terms of menstruation frequency at present.^[35]^ In order to reduce the placebo effect of sham-acupuncture, the expectation value of the acupuncture effect will be evaluated before treatment.

Furthermore, assessing the psychological index would be meaningful for the effectiveness evaluation. According to 1 study, women with PCOS had increased anxiety and depression, compared with women without PCOS.^[28]^ A systematic review also reported that PCOS diagnosis is associated with an increased risk of moderate and severe depressive and anxious symptoms.^[36]^ However, very few studies have currently examined the impact of the use of oral contraceptive pills on depressive and anxiety symptoms in women with PCOS.^[37]^ Thus, psychological function should be considered when assessing the effect of treatment.

In addition, PCOS affects the health-related QOL of patients.^[38]^ According to a systematic review, due to the small number of studies, restricted sample size, and the methodological diversity of the questionnaires used, there is a lack of detailed understanding of QOL that patients are facing.^[39]^ Assessing the effectiveness of treatment in terms of QOL should not be ignored. It is reliable and valid to use the Chinese version of PCOSQ for women with PCOS.^[5]^

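### Section 2.12.2 sets an unqualified P<.05 significance rule that takes in some 47 to 61 secondary comparisons and the phenotype subgroups; restricting it to the primary outcome is a cheap improvement

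*Protocol article*

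**What the plan says.** All places are in the protocol article.

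- **Decision rule (2.12.2).** After naming the t, Wilcoxon and chi-square tests for continuous and categorical data in general, the section says that a P "value <.05 will be considered statistically significant". The next sentence adds that "a subgroup analysis will be conducted according to these phenotypes". The outcomes to be analysed by phenotype are not named.
- **Primary outcome (2.10.1).** There is one: "The proportion of participants who have at least a 50% increase from baseline in monthly menstrual frequency after 3 months of intervention". Section 2.12.1 bases the sample size on it.
- **Secondary outcomes (2.11.1 to 2.11.7).** These include "the change in monthly menstrual frequency from baseline, to after 3 months of intervention, and 3 months postintervention follow-up", anthropometry ("height, weight, waist and hip circumference, body mass index (BMI), and waist-hip ratio (WHR) at month 3 and 6"), a hormone panel ending in "sex-hormone binding globulin (SHBG), and androstenedione (AND) from baseline at month 3 and 6", ovarian ultrasound ("Calculation changes in bilateral ovaries, mean difference in ovary volume, thickness of the endometrium, and the number of follicles <9 mm"), the FG and GAGS scores, HADS and PCOSQ. From anthropometry onward, each is assessed at months 3 and 6.
- **Aim.** Section 2.1 limits it to menstrual frequency. The Discussion (section 3, and the abstract's discussion paragraph) states it as efficacy and safety for "improving menstrual frequency and other symptoms of patients with PCOS". Section 3 also argues that mood and quality of life should count when the treatment effect is judged.

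The article gives no order of testing, no adjusted threshold and no statement that secondary or subgroup results are exploratory.

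**The concern.** The rule is a positive statement and, read plainly, makes no distinction between the primary comparison, a month-6 prolactin difference and a subgroup contrast. With dozens of comparisons each tested at 5%, some will probably cross the threshold by chance. Because the Discussion counts other symptoms among the things acupuncture is being evaluated for, such a result could be reported as a demonstrated benefit on hormones, mood or quality of life. What is at stake is the credibility of the secondary claims, not the primary conclusion.

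**Working it through.** **The plan's own figure.** The article states no error rate across secondary outcomes, so there is none to reproduce. Its 5% alpha appears only in the primary sample size (2.12.1: 35% versus 15%, 80% power, 71 per group). The arcsine formula n = 2(z₀.₉₇₅ + z₀.₈₀)²/h², with h = 2·arcsin√0.35 − 2·arcsin√0.15, gives 70.85, so 71 per group two-sided. That supports reading the 5% as two-sided; section 2.12.2 does not state sidedness.

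**Number of secondary comparisons.**

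| Section | Outcomes | Broad count | Narrow count |
|---|---|---|---|
| 2.11.1 | Follow-up responder proportion (1), change in frequency at two times (2) | 3 | 3 |
| 2.11.2 | Six measures × 2; narrow count drops height | 12 | 10 |
| 2.11.3 | Ten hormone measures × 2 | 20 | 20 |
| 2.11.4 | Four ovarian measures × 2, or three × 2 | 8 | 6 |
| 2.11.5 | FG, GAGS × 2 | 4 | 4 |
| 2.11.6 | Two HADS subscales × 2, or one score × 2 | 4 | 2 |
| 2.11.7 | Five PCOSQ domains × 2, or one score × 2 | 10 | 2 |
| Total | | 61 | 47 |

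**Independent tests, no true effect.** In either direction, the chance of at least one P<.05 among k tests is 1 − 0.95^k. For results favouring acupuncture, one tail of 2.5% applies, giving 1 − 0.975^k.

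- k = 61: 1 − 0.95^61 = 95.6% in either direction, with 61 × 0.05 = 3.05 expected. In favour of acupuncture: 1 − 0.975^61 = 78.7%, with 61 × 0.025 = 1.5 expected.
- k = 47: 91.0% and 69.6%, with 2.35 and 1.2 expected.

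**Correlated tests.** Independence is an upper case here: BMI, waist-hip ratio and LH/FSH are derived from other listed items, and months 3 and 6 repeat the same measures. The article gives no correlations, so these are assumptions. The figures come from simulating correlated normal test statistics, 100,000 draws, 61 tests.

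| Assumed correlation | Either direction | Favouring acupuncture |
|---|---|---|
| Common 0.3 | 85.5% | 48.7% |
| Common 0.5 | 66.7% | 34.1% |
| Blocks: 0.5–0.7 over time, 0.2–0.5 within domain, 0–0.2 between domains | 82.5% to 93.2% | 48.3% to 70.6% |

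A common correlation of 0.7 across all 61 tests would give 43.1% and 21.6%, but that is hard to credit between, say, height and a mood score. The expected numbers of false results (3.05 and 1.5) do not depend on correlation.

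**Clinical symptom outcomes only.** Menstrual frequency 3, FG/GAGS 4, HADS 4 and PCOSQ 10 make 21 tests. If independent: 1 − 0.95^21 = 65.9% in either direction and 1 − 0.975^21 = 41.2% in favour of acupuncture.

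**Subgroups.** Adding only three phenotype tests of the primary outcome (k = 64, treated as independent) gives 96.2% and 80.2%. The article does not say that more than this is planned.

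**The case against.** **This may be an omission rather than an error.** A multiplicity procedure for secondary outcomes is commonly left to the SAP or the full protocol, neither of which is shown, and the P<.05 sentence is a familiar nominal-threshold sentence. It does not say that a secondary P<.05 establishes efficacy. This stands in part: the absence of a multiplicity section is no finding. What remains is that the sentence as printed has no limit, follows tests named for all data types, and directly precedes the subgroup analysis. An SAP with a hierarchy would have to narrow it.

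**A reader might infer that a false benefit on other symptoms is close to certain.** The documents do not support that. The 96% counts differences in either direction and assumes independence. In favour of acupuncture the figure is at most about 79% for 61 tests, and lower under correlation. Many of the listed measures are not symptoms, or have no stated direction of benefit (height, prolactin, estrogen, endometrial thickness). For the 21 symptom comparisons the chance of a false benefit is about 41% even if they are independent.

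**A reader might also infer that the trial's main error rate is inflated.** It is not. There is one primary outcome with one comparison, it carries the sample size, and everything else is labelled secondary. Section 2.1 names menstrual frequency alone; the wider aim appears only in the Discussion and the abstract's discussion paragraph.

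**Conclusion.** The point holds as a minor, inexpensive improvement. Applied as printed to 61 secondary comparisons with no true effect, the rule would yield at least one significant result with a chance of about 67% to 96%, and at least one favouring acupuncture with a chance of about 34% to 79%. About 1.5 favourable false results would be expected. Even 34% is about 14 times the 2.5% for one two-sided test (34.1/2.5).

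These figures assume two-sided tests and a common correlation between 0.5 and 0. The narrow count of 47 lowers the independent-test figures to 91.0% and 69.6%. Subgroups would add to them by an amount that cannot be fixed, because their outcomes are not named. The conclusion about the primary outcome is unaffected.

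**What to change.** In section 2.12.2, replace the general threshold sentence with two:

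1. The P<.05 criterion is confirmatory for the primary outcome only.
2. All secondary and phenotype-subgroup comparisons are exploratory, are reported as estimates with 95% confidence intervals, and support no efficacy claim on their own.

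If the sponsor wants one secondary result to carry confirmatory weight, the follow-up responder proportion in 2.11.1 could be tested only if the primary comparison succeeds.

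The change needs no extra participants, data or analyses and leaves the sample size alone. Its one real cost is that, apart from any outcome placed in such a sequence, secondary outcomes can no longer be called statistically significant.
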